#### Outcome Variables and Measurement

In H2, we hypothesize that more layperson responders will indicate that they have received OEND programming and carry naloxone on their person within 6 and 12 months of initial contact using procedures in arm 2 (tailored messaging) compared to procedures in arm 1 (standard messaging) and using procedures in either arms 1 or 2 versus arm 3 (control). We will use several different data points to assess our hypothesis.

All push notifications sent out by first responder agencies already return information through the *PulsePoint* app indicating the total number of active devices, by type, that were messaged. As we explained previously, this is a strong proxy measure for the total number of active users messaged because most people use a single smartphone.

For purposes of computation, this total number of recipients of any push notification will be designated as *T*. Next, the total number of individuals who click on the pushed link will be represented by *O*, which will be a number between *0* and *T*. Importantly, the link will also be coded using HTML and CSS so that it sends additional data when clicked, indicating the originating community (cluster identity) and the data collection point (*D*, a value ranging from *0*, which is the initial push message cluster, to *2*, which is the final data collection message set at 12 months after baseline). Subsequently, the number of instances of an individual (ie, unique device) indicating that they have been trained on recognizing an overdose and administering naloxone (represented by *N*, a binary value of *0* or *1*) and whether they currently carry naloxone (represented by *C*, also a binary value of *0* or *1*) will be captured from the landing page itself.

This information will allow us to determine the following, separately by community:

At baseline, we will calculate the ratio of persons certifying that they are trained (numeric count of *N*) compared to the total number of push message recipients (*T*), the ratio of persons certifying that they carry naloxone (numeric count of *C*) compared to the total number of push message recipients (*T*), and the ratio of individuals who clicked on the link (*O*) compared to the total number of push message recipients (*T*).Separately at 6- and 12-month follow-ups, the numbers of certifications of training and carrying naloxone (*N* and *C*, respectively) that were submitted compared to the numbers of push recipients (*T*) in each period (tracked by *D*) and the ratio of individuals who clicked on the link (*O*) each month compared to the number of total push message recipients (*T*).Our outcome variables are ratios: *X = (N / T)* for each value of *D* (0, 1, or 2) and *Y = (C / T)* for each value of *D*. The ratio *Z = (O / T)* is a covariate representing engagement with push messages at each value of *D*.

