### H2: Layperson Responders

#### Overview

Layperson responders who are part of the *PulsePoint* system register with a local first responder agency using their smartphone. Most layperson responders (eg, those who are not also off-duty first responders themselves) are only alerted to incidents in public spaces. No identifying information is collected from these users except the unique ID of the device.

The first responder agency in each community that manages the *PulsePoint* subscription can only determine the number of active users and, broadly, the type of smartphone being used (eg, Android smartphone or iPhone). Each time a first responder agency sends out a push notification, it is provided with an exact count of the number of unique devices, separated by type, that were active in the system and reached by the message.

It is important to note that we will have a count of unique active devices but not necessarily a count of unique active users (eg, it is unlikely but possible that someone will install the app on 2 different mobile phones at the same time). In correspondence with the PulsePoint Foundation, it is likely that the count of unique active devices serves as a very close approximation of unique active users. Furthermore, by virtue of randomization, the distribution of any unmeasured anomalies related to user-device mismatches should be evenly distributed across the arms.

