Users randomized to arm 1 will receive standard monthly recruitment push messages. These push messages will differ from the certification messages because they will contain language intended to foster engagement with OEND services (eg, to get trained and carry naloxone) alongside the link to a landing page (eg, “Are you trained to recognize an overdose? Be a community hero! Click here for more information!”). The messages will be developed based on best practice recruitment principles in cooperation with an external marketing team and then reviewed and finalized by the study team. Messages will be different each month. The monthly time frame was selected based on our need to balance contact with responders and research or expert opinions on push messaging saturation. In a hypothesis-driven objective measure study, increased push messaging frequency was associated with additional app uninstalls *and* lower push message opening rates [68]. This information is generally consistent with the much larger volume of layperson marketing gray literature on push notification optimization (eg, *how-to* blogs [69]). Figure 3 displays the planned timing of the recruitment and data collection messages.

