**Figure 3 figure3:**
[figure not shown]
Push notification types and timing relative to agency recruitment. B: baseline.

The landing page for recruitment will be updated to include a link to the Community Overdose Responder naloxone training [70], which has been designed specifically for laypersons and integrates elements of OEND programming and *PulsePoint*. Where provided by community first responder agencies, we will also include a list of ways to obtain free or reduced-cost naloxone locally as well as information about upcoming local OEND events. Separately, we note that accessing at-cost naloxone (ie, not free or subsidized) will be relatively easy, in principle, given its transition to OTC status [22].

#### Layperson Intervention (Recruitment) Arm 2

As in the case of the differentiation between agency recruitment in arm 1 and arm 2, the recruitment of layperson responders for arm 2 will follow the same procedures that are described for arm 1 but will use separate messaging. Specifically, the push messages and landing page will contain additional, brief messages that specifically provide factual information that counteracts misperceptions about overdose and naloxone [39]; for example, whereas an example message for arm 1 might be “Are you trained to recognize an overdose? Be a community hero! Click here for more information!” the permutation for arm 2 might be “Are you trained to recognize an overdose? Studies show that most people revived with naloxone will not overdose again within the next year! Click here for more information!”

#### Layperson Intervention (Control) Arm 3

Arm 3 functions as the control arm and will not receive any monthly recruitment messaging or encouragement, but laypersons will still be asked, using push notifications, to provide information at baseline and 6 and 12 months later to document whether they have been trained to recognize an overdose and administer naloxone and whether they currently carry naloxone on their person (eg, “Please let us know whether you have ever been trained to recognize an overdose or if you carry naloxone by clicking here.”). The landing page will likewise contain the questions with radio button responses but will not link to training opportunities or contain additional information.

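### X and Y at 6 and 12 months divide by the devices still active then, a count that monthly pushes may change; report T by arm and a baseline-denominator sensitivity analysis

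*Protocol article*

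**What the plan says.** H2, Outcome Variables and Measurement, defines X = N/T (trained) and Y = C/T (carrying) for each data collection point D = 0, 1, 2. At follow-up, the certifications are those "that were submitted compared to the numbers of push recipients" of that wave, so the denominator is re-counted "in each period (tracked by" D) and is not fixed at baseline. T is "the total number of active devices, by type, that were messaged". The H2 Overview says that when an agency sends a push, "it is provided with an exact count of the number of unique devices, separated by type, that were active in the system" and reached.

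The arms differ in push exposure. Under Layperson Intervention (Recruitment) Arm 1, users receive a monthly recruitment push; arm 2 follows the same procedures with different content. Arm 3 "will not receive any monthly recruitment messaging or encouragement", but gets the certification pushes like everyone else.

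The Arm 1 section also cites a study in which "increased push messaging frequency was associated with additional app uninstalls" and with lower opening rates, and explains the interval chosen: "The monthly time frame was selected based on our need to balance contact with responders and research or expert opinions on push messaging saturation".

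In H2, Sample Size, Power, and Analysis, X and Y are analysed by generalized linear mixed models with Z = O/T (clicks over recipients) as a covariate. No missing outcome data are expected, because non-response counts as N = 0 or C = 0.

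**The concern.** A device that has uninstalled the app is in neither the numerator nor the denominator at the next wave. T at D = 1 and D = 2 can therefore be altered by the intervention whose effect it is used to measure. The evidence on push frequency informed the messaging interval but was not carried into the outcome definition.

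The safeguards in the text do not reach this. The missing-data rule covers only devices still counted in T. The H2 Overview relies on randomisation to balance mismatches between users and devices, but randomisation does not balance losses that follow from the assigned messaging.

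Two things are at stake. First, H2 is worded as more responders engaging, yet a ratio with a moving denominator can rise when the number of trained or carrying responders does not. Second, loss of active volunteer CPR responders bears on the feasibility aim in the Discussion and is a possible harm of scaling up. None of the stated outcomes or limitations covers change in T by arm.

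**Working it through.** **Inputs.** The definitions of X, Y, Z and T, the power parameters and the network size come from the article. It gives no certification rate, uninstall rate, click rate or between-agency SD; the values used for these below are assumptions.

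**1. The plan's own figure.** For a between-arm F test with 3 arms, m = 3 time points and correlation 0.5, the noncentrality is λ = f²·N·m/(1 + (m−1)·0.5).
- 50 agencies per arm (N = 150), f = 0.21: λ = 0.0441 × 150 × 3/2 = 9.92, power 0.804.
- 20 per arm (N = 60), f = 0.34: λ = 0.1156 × 60 × 3/2 = 10.40, power 0.810.

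Both stated effect sizes reproduce and are not in dispute.

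**2. All leavers are non-certifiers, no true effect.** If a share d of devices is lost, raw X becomes X/(1−d), a relative change of 1/(1−d) − 1. For d = 5%, 10%, 15% and 20% this is 5.3%, 11.1%, 17.6% and 25.0%.

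**3. Direction depends on who leaves.** Let p be the certification rate, u the extra loss among non-certifiers and v the extra loss among certifiers. Then X = p(1−v)/[p(1−v) + (1−p)(1−u)], and the ratio on baseline recipients is p(1−v). With p = 10% and u = 20%:

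| v | N_D/T_D | N_D/T_0 |
|---|---|---|
| 0% | 0.100/0.820 = 12.2% | 10.0% |
| 10% | 0.090/0.810 = 11.1% | 9.0% |
| 20% | 0.080/0.800 = 10.0% | 8.0% |
| 30% | 0.070/0.790 = 8.9% | 7.0% |

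If leaving is unrelated to certifying (v = u), the period ratio is undistorted. It also gives no sign that a fifth of responders are gone.

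**4. Ratio and count can disagree.** Take T_0 = 1000 in both arms. A messaged arm with 95 certifiers among 800 remaining devices has X = 11.9%; a control arm with 100 among 1000 has 10.0%. On T_0 these are 9.5% and 10.0%.

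**5. What adjusting for Z does.** Start from T = 1000, O = 200, N = 100, so X = 10% and Z = 20%. Remove 100 non-certifying devices, giving X = 100/900 = 11.1%.
- All 100 never click: Z = 200/900 = 22.2%. X and Z rise by the same factor and N/O stays at 50%, so adjustment can absorb the change.
- 50 of the 100 are clickers who do not certify: Z = 150/900 = 16.7%. Z falls while X rises, so adjustment does not remove the change.

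**6. Lower opening rates.** If 10% of devices leave (none certifiers) and lower opening also cuts certifications by 10%, X = 90/900 = 10.0%. The two effects cancel in the period ratio, while N_D/T_0 = 9.0%.

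**7. Size against the design.** Take arms at X/(1−d), X/(1−d) and X, with X = 10%. At d = 20% the standard deviation of the three means is 0.025 × √2/3 = 0.0118. Dividing by an assumed between-agency SD of 0.03, 0.05 or 0.10 gives f = 0.39, 0.24 or 0.12. At d = 10% and SD 0.05, f = 0.10; at d = 5%, f = 0.03 to 0.08. The stated f = 0.21 refers to an effect averaged over three time points. If the monthly pushes start after the baseline wave, the gap exists at only two of three, so the averaged value at d = 20% and SD 0.05 is about 0.24 × 2/3 = 0.16. Only a large, selective loss with a small SD would exceed 0.21 (0.39 × 2/3 = 0.26).

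**8. Scale of loss.** 1,085,000/755 ≈ 1437 users per agency. A 10% extra loss would be about 144 per agency, or about 5,700 responders over arms 1 and 2 with 20 agencies each and 14,400 with 50 each.

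**The case against.** The strongest reply is that the evidence does not show a bias in the intervention's favour, and this stands. The cited study is reported as an association, concerns increased frequency, and comes with no rate. The monthly interval was chosen with saturation in mind. The same sentence reports lower opening rates, which would push N/T down in the messaged arms. Arm 3 also receives certification pushes (an initial message and two reminders at each of three waves), so only extra loss in arms 1 and 2 matters. If leavers are people who never click, the planned adjustment for Z would largely absorb the artefact.

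That last point holds only in part. It fails when leavers are clickers who do not certify, and Z is itself measured after randomisation. A covariate also cannot show how many responders were lost.

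A second reply is that tabulating T by arm is the kind of detail a condensed article leaves to the analysis plan. This is fair as far as it goes: a reader might infer that the loss will go unreported, but silence in the article does not establish that. The formula for X and Y, however, is stated in the article, and its dependence on a post-randomisation count follows from it.

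A third reply is that a baseline denominator fits an open, anonymous user pool poorly. This also stands. If 100 users join a community of 1000 and 10% of everyone certifies, N_D/T_0 = 110/1000 = 11.0% while N_D/T_D = 110/1100 = 10.0%. The fixed-denominator ratio is thus not a strict proportion and mixes uptake with growth and retention.

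**Conclusion.** The point holds as a limit on interpretation. X and Y at 6 and 12 months rest on a denominator that the intervention may alter, and for the contrasts of arms 1 and 2 with arm 3 the ratio alone cannot separate more certified responders from fewer active devices. Distortion needs two conditions that the document neither shows nor excludes: extra device loss from monthly messaging, and leavers who differ from stayers in their chance of certifying. Under the assumption of 10% extra loss, all non-certifiers, raw X is 11% too high in relative terms; under other assumptions the error is zero or negative.

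A reader might infer that the contrasts with control are biased upward, or that an inflation of 5% to 25% is to be expected. The documents support neither: those figures come from assumed loss rates with every leaver a non-certifier. Arm 2 versus arm 1 shares one push schedule and is affected only if message content changes uninstalls. The power figures are unaffected. This is a cheap improvement that should be made; it does not undermine the design.

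**What to change.** - Keep N_D/T_D and C_D/T_D as the primary H2 outcomes.
- Add T_D/T_0 by arm at 6 and 12 months as a secondary feasibility and harm outcome.
- Prespecify N_D/T_0 and C_D/T_0 as a sensitivity analysis for the contrasts with arm 3, and interpret an H2 effect over control in the light of both ratios.

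No new data are needed, because T is returned with every push; the cost is a few lines in the plan and one extra table. The drawback is that users who join after baseline enter the numerator but not T_0. The fixed-denominator ratio should therefore be a companion to the period ratio, neither a replacement for it nor a condition for claiming an effect.

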#### Sample Size, Power, and Analysis

Our power analysis for H2 depends on the number of communities that agree to participate during the agency recruitment conducted as part of testing H1. To compare the average proportions of users who certify that they have received overdose education and personally carry naloxone, we sought 80% power to detect significant differences (2-tailed α=.05) among the 3 arms across 3 time points. Assuming a correlation of 0.5 in responses over time, we expect that we will be able to detect a medium effect size ranging from *f*=0.21 (if 50, 83% of the 60 communities participate in each arm on average) to *f*=0.34 (if 20, 33% of the 60 communities participate in each arm on average).

Our primary analyses will be metrics *X* and *Y* (as described previously), which will be analyzed separately. The primary analyses will be conducted using generalized linear mixed models, adjusting the *df* for the number of agencies. As with H1, we will report exact P values and commit to a cautious interpretation of the findings, avoiding overreliance on P values as the single arbiter of meaning [64]. In addition, as in the case of H1, we do not expect any missing data in the outcome variable because the nature of its computation is such that missing data mean that either *N*=*0* or *C*=*0* and are therefore built into outcome variables *X* and *Y*. Study covariates will include but may not be limited to variable *Z* to control for the conversion of push messages to clicks.

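### H2 is about 6 and 12 months, but its power basis averages baseline into the arm effect, and the baseline ratios are not named as covariates

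*Protocol article*

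**What the plan says.** In the H2 part of Methods, Outcome Variables and Measurement places the hypothesis at 6 and 12 months. It then states "Our outcome variables are ratios", with X=N/T (trained) and Y=C/T (carrying) defined at each of D=0, 1 and 2. D=0 is the baseline certification push, sent once an agency has signed its memorandum of understanding.

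Sample Size, Power, and Analysis gives the aim "To compare the average proportions of users who certify that they have received overdose education and personally carry naloxone" and says "we sought 80% power to detect significant differences", at a two-tailed alpha of 0.05, "among the 3 arms across 3 time points". It continues "Assuming a correlation of 0.5 in responses over time" and reports a detectable f of 0.21 ("if 50, 83% of the 60 communities participate in each arm on average") to 0.34 (20 per arm). The primary analyses are of X and Y separately, by generalized linear mixed models with degrees of freedom based on the number of agencies.

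The one covariate named for H2 is Z, the click ratio, included "to control for the conversion of push messages to clicks". The covariate list is left open. Baseline X or Y is not named as a covariate, and neither an arm-by-time term nor a change-from-baseline contrast is mentioned.

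**The concern.** D=0 is collected before the monthly messaging has had time to act, so it should carry little or none of the effect that H2 is about. Averaging it into the arm comparison shrinks a real follow-up effect and leaves each agency's starting level in the contrast. The same measurement used as a covariate would remove part of that between-agency variation.

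Starting levels matter more here than in an ordinary randomized comparison. H2 analyses only agencies that agreed to join, after being recruited with arm-specific material. The Discussion concedes that uptake in arm 3 is uncertain because participation brings those communities no direct benefit, but it draws a consequence only for power. If different kinds of agency join in different arms, baseline levels can differ systematically. How baseline enters the model then decides how much of that gap is read as a messaging effect.

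**Working it through.** **Inputs from the H2 sample-size section.** 3 arms; m=3 waves; correlation r=0.5; two-tailed alpha 0.05; 80% power; n=50 or 20 agencies per arm (N=150 or 60).

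**1. Reproducing the stated f.** For the arm main effect in a repeated-measures ANOVA, λ = f²·N·m/(1+(m−1)r), with 2 and N−3 degrees of freedom.
- 50 per arm: 0.21²×150×3/2 = 9.92, power 80.4%.
- 20 per arm: 0.34²×60×3/2 = 10.40, power 81.0%.

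Detectable f at 80% power under the candidate contrasts:

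| Contrast | 50 per arm | 20 per arm |
|---|---|---|
| Stated in the article | 0.21 | 0.34 |
| Arm main effect, three waves | 0.209 | 0.336 |
| Arm main effect, two follow-ups | 0.222 | 0.356 |
| Single wave | 0.256 | 0.412 |
| Arm-by-time interaction | 0.116 | 0.186 |

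Of these, only the three-wave average matches.

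**2. Efficiency of each contrast.** Assume unit variance at each wave, equal correlation r, no arm effect at D=0, the same effect d at both follow-ups, and no role for Z. At r=0.5:

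| Contrast | Effect | Variance | Effect/SD | Information per d² |
|---|---|---|---|---|
| Three-wave mean | 2d/3 | (1+2r)/3 = 0.667 | 0.816d | 0.667 |
| Follow-up mean, unadjusted | d | (1+r)/2 = 0.75 | 1.155d | 1.333 |
| Follow-up mean minus baseline | d | (1+r)/2+1−2r = 0.75 | 1.155d | 1.333 |
| Follow-up mean, baseline as covariate | d | (1+r)/2−r² = 0.50 | 1.414d | 2.0 |

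Adjustment gains 2.0/1.333 = 1.5-fold in effective agencies over either unadjusted follow-up or change, and 2.0/0.667 = 3.0-fold over the three-wave mean.

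For an assumed r of 0.3 and 0.7, the gains are:
- against unadjusted follow-up: 1.16 and 2.36;
- against change: 1.87 and 1.25;
- against the three-wave mean: 2.14 and 5.0.

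**3. Pairwise power at d=0.5 SD (assumed), r=0.5.** Power = Φ(ratio×0.5/√(2/n) − 1.96), where ratio is the multiplier of d in the Effect/SD column.

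| | 20 per arm | 50 per arm |
|---|---|---|
| Three-wave mean | 0.25 | 0.53 |
| Unadjusted follow-up, or change | 0.45 | 0.82 |
| Baseline-adjusted follow-up | 0.61 | 0.94 |

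**4. The same in the plan's f.** The follow-up f detectable at 80% power is:
- three-wave mean: 0.314 (50 per arm) and 0.504 (20 per arm), which is 1.5 times the 0.209 and 0.336 above;
- unadjusted follow-up: 0.222 and 0.356;
- baseline-adjusted: 0.181 and 0.291.

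**5. A stable baseline gap.** A gap g present at all three waves enters the three-wave mean and the unadjusted follow-up mean as g. It enters the adjusted contrast as g(1−r) = 0.5g and the change contrast as 0. Simulation with an assumed gap of 0.3 SD in one arm and no true effect (4,000 runs per setting) gave these rejection rates at the 5% level:

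| | 50 per arm | 20 per arm |
|---|---|---|
| Three-wave mean | 45% | 20% |
| Unadjusted follow-up | 41% | 18% |
| Baseline-adjusted | 17% | 9% |
| Change from baseline | 5% | 4% |

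**The case against.** The strongest reply is that the article does not state the model in enough detail to be wrong. It lists no fixed effects, does not say which term is tested, and leaves the covariate list open. A condensed article may leave these to an analysis plan. Defining X and Y at D=0 is no defect in itself, since a model with arm-by-time terms also has baseline among its outcomes. The words about three time points come from the power sentence, and the averaging mentioned there may be over agencies rather than waves. A power approximation does not bind the analysis.

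Much of this stands. A reader might infer that the primary model definitely pools baseline, or that adjustment was considered and rejected. The article does not say either. Pooling is inferred from the power figures, and the 3.0-fold gain belongs to that inference alone. Under a change contrast a stable gap would cancel, so the statement that it enters in full would not apply.

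Two further limits also stand. Z is tied to X and Y because certifying requires reaching the landing page. It may absorb some agency differences, and the correlation remaining after Z is not given. D=0 is also measured after arm-specific agency recruitment. The general description of the baseline landing page includes introductory text that the arm 3 description appears to exclude, so baseline may not be wholly untouched by arm.

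The reply does not remove the point. The waves, the named covariate and the power basis are stated choices, and they do not line up with a hypothesis about 6 and 12 months. The 1.5-fold gain at r=0.5 holds against both alternative contrasts.

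**Conclusion.** The point holds in a limited form and is worth acting on. H2 is a follow-up hypothesis whose stated power fits only a three-wave average including baseline, and the plan does not commit to using the baseline ratios as covariates. The secure gain from doing so is 1.5-fold in effective agencies at the plan's r=0.5, and 1.16- to 2.4-fold against unadjusted follow-up for an assumed r of 0.3 to 0.7. It is 3.0-fold only if the three-wave average is what will be tested. These figures assume no arm effect at D=0, equal effects at both follow-ups, and no contribution from Z.

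A reader might also infer that baseline adjustment cures selective joining, or that a mixed model with one common baseline mean would serve equally well. Neither follows. Adjustment only about halves a stable gap at r=0.5. A common baseline mean is not assured by randomization, because agencies enter H2 after arm-specific recruitment.

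**What to change.** - State the primary H2 contrasts as the arm comparisons at D=1 and D=2, with the agency's D=0 value of X (or Y) as a covariate on the model's link scale.
- Say that D=0 is not pooled into the arm effect, and do not constrain the arms to a common mean at D=0.
- Restate the detectable effect for this contrast. At r=0.5, with Z ignored and the two follow-ups averaged, it is f=0.181 with 50 agencies per arm and 0.291 with 20.
- Report change from baseline as a sensitivity analysis, because covariate adjustment reduces a systematic baseline gap without removing it.

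The cost is wording and one degree of freedom. The baseline ratios are already to be collected.

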#### Hypotheses

We will test the following hypotheses:

H1: more first responder agencies will be successfully recruited by arm 2 than by arm 1.H2: more layperson responders will report engaging with OEND programming in arm 2 than in arms 1 or 3 and in arm 1 than in arm 3.

As an exploratory follow-up, we will conduct incentivized qualitative follow-up interviews with agencies to better understand barriers to participation and how to improve uptake feasibility.

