The *PulsePoint* app is structured in such a way that push notification hyperlinks can open an external web page in a web browser window inside the app. Using the style guides and templates from the PulsePoint Foundation, the certification web pages will be designed to be similar to the appearance of the app to avoid disrupting the user experience while avoiding cross-contamination of messaging between the study arms. Each web page will be accessible only via the hyperlink in its associated push notification, and users will not be able to navigate among web pages or access the web pages for other study arms.

As multiple data collection reminders will be sent each time (baseline, 6 months, and 12 months), we want to minimize the likelihood of an individual repeatedly certifying their involvement. This risk exists because of the completely anonymous way that individual *PulsePoint* users are managed by the system. Thus, the landing page will be configured to store a cookie [67] on the mobile device. Although cookies are typically perceived as tracking devices, this cookie will not *record anything except whether the user has previously responded to either question on the landing page* during the data collection cycle, and it will be programmed to delete itself after each data collection period (eg, 3 weeks). When users who have already completed the questions return to the landing page, the cookie will prevent the questions from being displayed, although we anticipate that some of the users may clear their smartphone browser cache or actively prevent the use of cookies.

#### Layperson Intervention (Recruitment) Arm 1

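### The H2 primary models adjust for the follow-up click ratio Z, which is measured after arm-specific messaging and is a factor of X and Y, so they do not estimate the all-recipient effect that H2 states

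*Protocol article*

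**What the plan says.** H2 (Hypotheses) is that "more layperson responders will report engaging with OEND programming in arm 2 than in arms 1 or 3 and in arm 1 than in arm" (the quote stops just before the number of the control arm, 3). The H2 section Outcome Variables and Measurement makes this operational as X = N/T and Y = C/T. Each is computed per community at D = 0 (baseline), 1 (6 months) and 2 (12 months), with every push recipient in the denominator. The same section says that Z = O/T "is a covariate representing engagement with push messages at each value of" D.

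The H2 section Sample Size, Power, and Analysis names X and Y as the primary metrics and generalized linear mixed models as the primary analysis. In the same paragraph it lists Z as a covariate, "to control for the conversion of push messages to clicks". It describes no primary model without Z and gives no direct-effect or mediation rationale.

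On the certification route, Conceptualizing Recruitment for Layperson Responders says: "Each web page will be accessible only via the hyperlink in its associated push notification". N and C are recorded on that page. Arms 1 and 2 receive monthly recruitment messages between certification rounds; arm 3 receives none.

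**The concern.** A covariate in a randomised comparison should be something that the allocated arm cannot change. Z at D = 1 and D = 2 is not: by then two arms have had months of push messages and the third has had none. Z is also arithmetically part of the outcome, because nobody can certify without opening the page. Holding it fixed leaves roughly the arm contrast in certifications per click, among people who selected themselves by clicking. H2 asks a different question: whether more of those messaged certify.

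Both H2 primary metrics and all three arm contrasts are affected. The abstract says that the best-performing approach will go forward to the next phase, so a distorted arm contrast could influence that choice.

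**Working it through.** **1. The plan's own figure.** For the H2 comparison the article says "we sought 80% power to detect significant differences (2-tailed α=.05) among the 3 arms across 3 time points". Its input for the repeated measures is given as follows: "Assuming a correlation of 0.5 in responses over time". The detectable effect is put at f = 0.21 in the favourable case, "if 50, 83% of the 60 communities participate in each arm on average", while in the unfavourable case it is f = 0.34, "if 20, 33% of the 60 communities participate in each arm on average". Take the between-arm F test of a repeated-measures ANOVA with m = 3 time points and ρ = 0.5, so that λ = f²·N·m / (1 + (m − 1)ρ), with 2 and N − 3 degrees of freedom.

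- 50 per arm: N = 150, λ = 0.0441 × 150 × 3 / 2 = 9.92, power 80.4%.
- 20 per arm: N = 60, λ = 0.1156 × 60 × 3 / 2 = 10.40, power 81.0%.

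The stated figures reproduce. No covariate enters them, so they describe the arm effect without Z.

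**2. The identity.** Certification needs a click, so N ≤ O and C ≤ O. With O counted on the certification link, X = N/T = (O/T) × (N/O) = Z × (N/O), and likewise Y = Z × (C/O). This follows from the definitions and needs no assumed rate.

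**3. What adjustment does.** Write z for an arm's click rate and q for its certifications per click. In a linear model, adjusted effect = ΔX − b·ΔZ, where b is the pooled within-arm slope of X on Z. If agencies vary by the same proportion in every arm, b is approximately Σz²q / Σz².

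**4. Numbers.** The article gives no click or certification rates, so all z and q below are assumptions. The contrast is arm 2 minus arm 3; triples are arms 3/1/2. The last column is the mean from 1,000 simulated three-arm trials per row (50 agencies per arm, 1,000 recipients each, log-SD 0.3 for both rates, least squares at one time point).

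| Case | z (%) | q (%) | ΔX | b | ΔX − b·ΔZ | Simulated, without Z → with Z |
|---|---|---|---|---|---|---|
| A. Effect through clicks only | 10/15/20 | 40/40/40 | +0.040 | 0.400 | 0.000 | +0.040 → 0.000 |
| B. Clicks rise, yield falls | 10/15/20 | 45/40/36 | +0.027 | 0.385 | −0.012 | +0.027 → −0.012 |
| C. Click rates equal | 15/15/15 | 30/40/50 | +0.030 | 0.400 | +0.030 | +0.030 → +0.030 |
| D. Both rise | 10/13/16 | 35/40/45 | +0.037 | 0.415 | +0.012 | +0.037 → +0.012 |
| E. Clicks fall, yield rises | 20/15/15 | 30/45/50 | +0.015 | 0.393 | +0.035 | +0.015 → +0.034 |

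Worked example, case B: b = (0.01 × 0.45 + 0.0225 × 0.40 + 0.04 × 0.36) / 0.0725 = 0.0279 / 0.0725 = 0.385, and 0.027 − 0.385 × 0.10 = −0.012. In case A the arm 2 versus 3 test rejects in 100% of trials without Z and 5% with it. The pattern is the same with 20 agencies per arm.

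**5. Lower rates, two arms.** With clicks of 5% versus 8% and q = 50% in both arms, ΔX = 0.040 − 0.025 = +1.5 points, b = 0.50, and the adjusted effect is 1.5 − 0.50 × 3 = 0.0 points. With q = 50% versus 45%, ΔX = 3.6 − 2.5 = +1.1 points, b = (0.0025 × 0.50 + 0.0064 × 0.45) / 0.0089 = 0.464, and the adjusted effect is 1.1 − 0.464 × 3 = −0.3 points.

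**6. Not an artefact of least squares.** With a binomial logit model and 33 agencies per arm, the odds ratio falls from 1.62 to 1.06 in the first case of step 5, and from about 1.47 to 0.95 in the second.

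**The case against.** The strongest defence is that a click on the certification link is also a response to a two-question survey. Non-response is scored as zero, so X and Y mix training or carriage with willingness to answer. On that view Z corrects for differential response, and the unadjusted +1.5 points in step 5 could arise with no additional person trained. The premise stands: unadjusted X and Y do combine the two. The remedy does not follow, because conditioning on Z says nothing about non-clickers and only moves the comparison to self-selected clickers. H2 is worded in terms of what responders report, with all recipients in the denominator.

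Second, the monthly messages that invite a click are recruitment messages, which the article separates from certification messages. A reader might infer from their wording that the intervention is built to raise Z. The documents do not support that: the stated aim is training and carriage, and the study cited on push frequency found lower opening rates with more frequent messages. The direction is therefore open. It remains that Z is measured after messaging that differs by arm.

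Third, the article mentions clicks in each month while indexing Z by D. If O counted monthly recruitment clicks, the identity in step 2 would not hold. Z would still be measured after randomisation, and arm 3 would have no counterpart because it gets no such messages.

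Fourth, this is a feasibility trial that promises cautious use of P values, and the community-level ratios are computed in any case, so unadjusted results can be recovered. That limits the harm but does not make the planned primary model match H2.

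**Conclusion.** The concern holds. Including Z at D = 1 and D = 2 means that the primary models for X and Y do not estimate the effect among all recipients that H2 states. This rests on the article's definitions and on O counting certification-link clicks.

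Size and direction are not determined by the documents. If the arms differ in click rate, the arm effect can be removed, reversed or inflated; if click rates are equal, nothing changes. The figures above are illustrations under assumed rates, mostly from a single-time-point linear model, and are not power figures for this trial.

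A reader might go further and infer that the adjustment will necessarily hide a benefit, or will usually show a significant effect of the wrong sign. The documents do not support either. They give no click rates, and their one cited finding on message frequency points to lower opening in the messaged arms, where adjustment would inflate the effect. How often a reversed effect reaches significance depends on assumed variation between agencies: at 33 per arm, with clicks of 5% versus 8% and yield of 50% versus 45%, simulations ranged from about 20% to 53%.

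**What to change.** - Remove Z at D = 1 and D = 2 from the primary models for X and Y.
- Adjust for the rurality stratum used in randomisation and, if wanted, the agency's own D = 0 ratio. Note that D = 0 precedes the monthly messages but follows arm-specific agency recruitment and signing of the memorandum of understanding. It is a safer covariate, not a pre-randomisation one.
- Report follow-up Z by arm as a secondary engagement or response outcome, and state which clicks O counts.
- Keep any Z-adjusted model as a labelled sensitivity or mediation analysis.
- State that unadjusted X and Y combine certification with willingness to respond.

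The cost is a few sentences in the analysis section. Data collection and sample size do not change. The article reports no data collection at submission; if collection has since begun, the change should be dated and made before arm-level results are seen.
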